### Participant recruitment

Potentially eligible patients will be identified by a treating physician, and approached by a study nurse. Accrual is expected to be complete within 2.5 years after trial initiation.

### Study procedures

Twelve visits are scheduled for this trial and a summary of study procedures for each visit is presented in Table 3. The expected duration of study participation is about 4–5 months. All patients must agree to use two reliable, effective contraceptive methods simultaneously for at least 7 days prior to the first dose of the study drug and for 6 weeks following the last dose of the study drug, unless absolute sexual abstinence is the chosen method of contraception. This is because mycophenolate mofetil is known to cause a high frequency of miscarriage (~ 50%) and severe birth defect in the unborn baby [26, 27].

**Table 3 Tab3:** Scheduled visits and assessments

Procedures	Study Visits											
	SV	C_1_w_0_	C_1_w_1_	C_1_w_2_	C_1_w_4_	C_2_w_2_	C_2_w_4_	C_3_w_2_	C_3_w_4_	C_4_w_2_	C_4_w_4_	FV
Informed consent obtained	×											
Inclusion/exclusion criteria assessments	×											
History taking	×											
Physical examination	×	×	×	×	×	×	×	×	×	×	×	×
ECOG status	×											
Electrocardiogram	×											
Lab test for complete blood count	×			×	×	×	×	×	×	×	×	×
Lab test for fasting blood glucose	×											
Other lab tests^(a)^	×			×	×		×		×		×	×
Circulating tumor cells		×^(b)^	×^(b)^	×		×		×		×		
Biobank collection	×				×		×		×		×	×
Urine analysis^(c)^	×			×	×		×		×		×	×
Stool examination	×											×
Pharmacokinetic study^(d), (e)^		×	×									
Pain score & Quality of life		×			×		×		×		×	×
Review of concomitant medications	×	×	×	×	×	×	×	×	×	×	×	×
Monitoring for adverse events			×	×	×	×	×	×	×	×	×	×
Tumor assessment^(f)^	×						×				×	

SV = screening visit; C_x_w_y_ = cycle x week y; FV = final visit. ^(a)^ Lab tests include Na, K, Cl, HCO3, Ca, Mg, P, albumin, AST, ALT, ALP, total bilirubin, direct bilirubin, BUN, Cr, PT, PTT, INR, and LDH; ^(b)^ Blood obtained from the pharmacokinetic study will be used for measurement of circulating tumor cells on C_1_W_0_ and C_1_W_1_ so that no additional blood samples will be collected; ^(c)^ Urine analysis includes a urine pregnancy test for a female patient of childbearing age; ^(d)^ Blood samplings (at 0, 0.5, 1, 1.5, 2, 3, 4, 6, 8, 10, and 12 h); ^(e)^ Additional samplings for drug monitoring may be required when drug dosage is modified (after ≥7 days of drug administration with an adjusted dose level); ^(f)^ Tumor assessment by a computerized tomography (CT) scan (of the chest ± other organs, if required) or magnetic resonance imaging (MRI), done at baseline, 8 ± 1 weeks and 16 ± 1 weeks after initiation of study drug administration; in case of objective tumor response (complete response or partial response), confirmatory imaging studies will be performed at least 4 weeks after initial documentation of response

There are three drug regimens to be used for prophylaxis of possible infection during study participation: (1) ivermectin (12 mg/day) for 2 days before Cycle 1, Week 0 [28], (2) trimethoprim-sulfamethoxazole (160/800 mg/day) once daily from Cycle 1, Week 1, until discontinuation of mycophenolate mofetil [29], and (3) acyclovir (400 mg/day) twice daily from Cycle 1, Week 1, until discontinuation of mycophenolate mofetil [30]. No evidence of PK drug-drug interactions between any of these regimens and mycophenolate mofetil is reported [31].

Should mycophenolate mofetil prove beneficial to some patients (i.e., evidence of stable disease or partial response) at the end of the treatment period (on Week 16), the study treatment will be given to those patients in the extension period until one of the withdrawal criteria is met. Additional visits will be scheduled during the extension period (Table 4).

**Table 4 Tab4:** Additional visits and assessments in the extension period

Procedures	Study Visits								
	C_5_w_2_	C_5_w_4_	C_6_w_2_	C_6_w_4_	C_7_w_2_	C_7_w_4_	C_x_w_2_	C_x_w_4_	FV
Physical examination	×	×	×	×	×	×	×	×	×
Lab test for complete blood count	×	×	×	×	×	×	×	×	×
Other lab tests^(a)^		×		×		×		×	×
Circulating tumor cells	×		×		×		×		
Biobank collection		×		×		×		×	×
Urine analysis^(b)^		×		×		×		×	×
PK study^(c)^									
Pain score & Quality of life		×		×		×		×	×
Review of concomitant medications	×	×	×	×	×	×	×	×	×
Monitoring for AEs	×	×	×	×	×	×	×	×	×
Tumor assessment^(d)^						×			

C_x_w_y_ = cycle x week y; FV = final visit. ^(a)^ Lab tests include Na, K, Cl, HCO3, Ca, Mg, P, albumin, AST, ALT, ALP, total bilirubin, direct bilirubin, BUN, Cr, PT, PTT, INR, and LDH; ^(b)^ Urine analysis includes a urine pregnancy test for a female patient of childbearing age; ^(c)^ Additional samplings for drug monitoring (at 0, 0.5, 1, 1.5, 2, 3, 4, 6, 8, 10, and 12 h) may be required when drug dosage is modified (after ≥7 days of drug administration with an adjusted dose level); ^(d)^ Tumor assessment by a CT scan (of the chest ± other organs, if required) or MRI, done at 12-week interval (±1 week); in case of objective tumor response (complete response or partial response), confirmatory imaging studies will be performed at least 4 weeks after initial documentation of response

The final visit will be scheduled in 4 weeks (±1 week) after the treatment with mycophenolate mofetil has stopped. After completion of the study, follow-up survival information will be collected by either clinical visit or telephone contact every 12 weeks (±1 week) until death.

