### Statistical analysis plan

All patients who receive at least one dose of mycophenolate mofetil will be included in an intention-to-treat analysis. Patients’ baseline demographics will be summarized using descriptive statistics. Study drug administration will be described in terms of the total number of cycles (or days) administered, the median (range) of cycles (or days) administered, dose intensity, and reasons for deviations from planned therapy. Adverse events will be collected after the patient has taken the first dose of mycophenolate mofetil.

The PFS at 16 weeks or DCR (the primary endpoint) will be measured as a binary variable: DCS or DCF. The PFS and OS will be summarized using the Kaplan-Meier method and displayed graphically as appropriate. For patients lost to follow-up, they will be censored at the date of the last follow-up visit. Median PFS and OS (and their corresponding 95% confidence intervals) will also be provided.

All statistical analysis will be executed using IBM SPSS Statistics for Windows, version 22.0, with a *p* value of less than 0.05 considered to indicate statistical significance. It is possible that the decision rule of this single-arm, two-stage phase II clinical trial may need to be adapted from the original plan [33]. If the attained sample size at the end of this study is different from the one that is initially planned due to any reason, a statistical testing will be conducted by calculating the *p* value with the sample size at the stopping stage conditioned on the observed value [34, 35]. The Jennison-Turnbull confidence interval may be used by treating the observed sample size at the stopping stage like the planned sample size [36].

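### Table 3 schedules no pregnancy test at C1w0, the apparent first-dose visit; after screening, the next test is about two weeks into dosing

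*Protocol article*

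**What the plan says.** All references are to the Protocol article.

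- **Where the test sits.** Footnote (c) to Table 3 (Study procedures) reads: "Urine analysis includes a urine pregnancy test for a female patient of childbearing age". The urine analysis row is marked at SV, C1w2, C1w4, C2w4, C3w4, C4w4 and the final visit (FV). It is blank at C1w0, C1w1, C2w2, C3w2 and C4w2.
- **Eligibility.** The row "Inclusion/exclusion criteria assessments" is marked at SV only. The Exclusion criteria rule out a pregnancy that is known or suspected.
- **Contraception.** Study procedures requires two methods together, or abstinence, "for at least 7 days prior to the first dose of the study drug" and for six weeks after the last dose.
- **Reason given.** The same section states that "mycophenolate mofetil is known to cause a high frequency of miscarriage (~ 50%) and severe birth defect in the unborn baby".
- **If pregnancy occurs.** It is listed under Withdrawal criteria.

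The article gives no maximum interval between SV and the first dose.

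**The concern.** For a drug with this reproductive risk, the useful moment for a pregnancy test is just before the first dose, when a positive result still prevents exposure. The schedule has one earlier test, at SV, and one later test, at C1w2, but none at the visit where dosing appears to start.

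Two kinds of pregnancy could pass through unseen: a conception too recent to show at SV, and a conception after SV but before contraception begins. Either would have no scheduled test until about two weeks into treatment. By then the remaining step is withdrawal, and the exposure has already happened.

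The matter is one of participant safety. Patients are eligible from age 13, and the article describes the affected population as mainly teenagers and young adults, so female patients of childbearing age should be expected.

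**Working it through.** There is no stated figure to reproduce, so the check reads the schedule and dates the visits.

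**1. Urine analysis row against the 12 visit columns of Table 3**

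| SV | C1w0 | C1w1 | C1w2 | C1w4 | C2w2 | C2w4 | C3w2 | C3w4 | C4w2 | C4w4 | FV |
|---|---|---|---|---|---|---|---|---|---|---|---|
| × | – | – | × | × | – | × | – | × | – | × | × |

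The row has a full set of 12 cells, so the blanks do not come from a shifted column. Seven of the 12 visits carry the test: one before C1w0, none at C1w0, and the next at C1w2. The C1w0 column is otherwise in use (physical examination, circulating tumor cells, PK, pain and quality of life, concomitant medications).

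**2. Is C1w0 the first-dose visit?** The article does not say so outright. Four items support it.

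- *Tumor assessment.* Footnote (f) has imaging "done at baseline, 8 ± 1 weeks and 16 ± 1 weeks after initiation of study drug administration", and Table 3 marks it at SV, C2w4 and C4w4. With 28-day cycles counted from C1w0, C2w4 = 2 × 28 = 56 days = 8 weeks and C4w4 = 4 × 28 = 112 days = 16 weeks. Both match, so drug initiation falls at C1w0 (day 0) and C1w2 is day 14.
- *PK.* The 12-hour profile in footnote (d), "Blood samplings (at 0, 0.5, 1, 1.5, 2, 3, 4, 6, 8, 10, and 12 h", is marked first at C1w0.
- *Prophylaxis.* The antiparasitic pre-treatment is timed to this visit: "ivermectin (12 mg/day) for 2 days before Cycle 1, Week 0".
- *Adverse events.* The Statistical analysis plan section says "Adverse events will be collected after the patient has taken the first dose of mycophenolate mofetil", and the monitoring row is blank at SV and C1w0 and starts at C1w1.

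**3. Length of the gap.** Let G be the days from SV to the first dose. G is not stated, so 7 and 14 days are assumptions. The 14-day limit on organ-function tests in the Inclusion criteria runs to enrollment, not to the first dose, and is only an analogue.

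- *Time between the two tests on either side of the first dose* = G + 14: 21 days at G = 7 and 28 days at G = 14.
- *Route 1, conception between SV and the start of contraception.* If contraception starts on the last permitted day (day −7), the open days are max(0, G − 7): 0 at G = 7 and 7 at G = 14. If it starts at SV, the result is 0 for any G.
- *Route 2, conception too recent to detect at SV.* This is possible at any G. It cannot be quantified because the article gives no detection lag.

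A patient who starts contraception only after SV must use it for at least 7 days before dosing, so G is at least 7 and her SV test is at least 7 days old at the first dose.

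**4. Comparison with later cycles.** Under Interventions, a new cycle begins only once safety assessments are done. The tests at C1w4, C2w4 and C3w4 fall where cycles 2, 3 and 4 begin. Cycle 1 is the only one of the four planned cycles with no pregnancy test at its starting visit.

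**The case against.** A fair defense is that nothing in the article is contradicted. A pre-dose test exists, at SV, and no statement in the document requires one on the day of dosing. The SV-to-dose window, and any rule to repeat screening tests after a delay, may well stand in the full protocol. Blood count and chemistry are also taken at SV and not at C1w0, so the design uses SV results as its baseline throughout. Route 1 vanishes if contraception starts at SV or if G is 7 days, and Route 2 has no number attached. Double contraception, the exclusion of suspected pregnancy and the C1w0 physical examination all lower the risk. A C1w0 test could itself miss a very recent conception.

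Most of this stands as a limit on size. The missing window can be put down to condensation, but the blank C1w0 cell cannot: it is printed in a schedule that fills other cells of that column. The safeguards reduce the chance of an undetected pregnancy, but none of them is a test. A short interval narrows Route 1 and leaves Route 2 open. That a C1w0 test would be imperfect is a reason to keep the C1w2 test as well; it does not justify omitting the earlier one.

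**Conclusion.** The concern holds as a weakness in the safety schedule. As printed, a female patient of childbearing age has one pregnancy test before dosing, of unstated maximum age, and the next at about day 14 of exposure. This rests on C1w0 being the first-dose visit, an inference with good support.

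The practical size is small and partly unknown. Few patients would be affected. Route 1 is open for 0 to 7 days over the assumed range of G from 7 to 14 days, and Route 2 is not quantified. The harm in an affected case could be irreversible, by the article's own account of the drug. Sample size, primary endpoint and error rates are unaffected. The change should be made, but it does not put the trial's conclusions in doubt.

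**What to change.** Mark a urine pregnancy test at C1w0 in Table 3 for female patients of childbearing age, and require a negative result before the first dose. Keep the C1w2 test, since a very recent conception may still be missed at C1w0.

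The cost is one mark in the table and one urine strip per eligible patient at an existing visit. The upper bound is 27 strips for the planned 27 patients, plus one for each replaced patient; the true number is lower because not every patient is a female of childbearing age. The downside is a rare late screen failure.

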### Withdrawal criteria

More than 4 weeks of study drug interruption due to toxicity;Disease progression or any significant deterioration in the health of the patient;Unacceptable toxicity;Occurrence of another illness which precludes further participation in this trial;Significant protocol noncompliance;Development of an illness or situation which would affect assessments of clinical status and study endpoints to a significant degree;Pregnancy;Patient lost to follow-up; orWithdrawal of informed consent.

Patients who withdraw or are withdrawn prematurely will be replaced only if they discontinue during the first four weeks due to reasons other than toxicity.

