### Sample size determination

The sample size was calculated according to the Simon’s minimax two-stage design, with PFS at 16 weeks as the primary endpoint. PFS is dichotomized according to whether PFS is ≤16 weeks (defined as disease control failure (DCF)) or > 16 weeks (defined as disease control success (DCS)). Therefore, treatment with mycophenolate mofetil will be considered successful if the 16-week radiological evaluation indicates stable disease, partial response, or complete response, as defined by the RECIST criteria version 1.1. Patients alive after 16 weeks without signs of progression will be regarded as DCS.

The sample size was calculated under a hypothesis of interest in which DCS at 16 weeks is ≥32% (*p*_1_ = 0.32, the minimal proportion of successes that makes the experimental treatment worth further studies) and a null hypothesis in which mycophenolate mofetil reaches a DCS at 16 weeks < 12% (*p*_0_ = 0.12, the proportion of successes that implies no clinically worthwhile activity of the experimental treatment). Setting *α* = 0.10 (where *α* represents the probability of failing to reject a treatment with response probability ≤*p*_0_) and *β* = 0.10 (where *β* represents the probability of rejecting a treatment with response rate ≥ *p*_1_), this condition requires 19 patients to be enrolled in Stage 1. Recruitment will continue to reach a total of 27 patients if the number of DCS among the first 19 patients is at least 3; otherwise, the trial will be stopped for inefficacy after analysis of 19 patients. As per the study protocol, mycophenolate mofetil will be deemed promising and worth further studies if at least 6 DCS is observed at the end of the study.

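### Patients who stop mycophenolate without documented progression have no scheduled tumour assessment at the final visit and only survival follow-up after it, so secondary Kaplan-Meier PFS misses their later progression

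*Protocol article*

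**What the plan says.** **Endpoint.** PFS as a time-to-event variable is a secondary endpoint (Study endpoints). Under Statistical analysis plan, "The PFS and OS will be summarized using the Kaplan-Meier method", with medians and 95% confidence intervals. The only censoring rule given there is for patients lost to follow-up, who are censored at their last follow-up visit.

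**Leaving treatment.** One withdrawal criterion reads "Disease progression or any significant deterioration in the health of the patient". Others cover unacceptable toxicity, more than four weeks of interruption for toxicity, intercurrent illness and noncompliance. None of these requires RECIST progression. The same criteria govern the extension, where "the study treatment will be given to those patients in the extension period until one of the withdrawal criteria is met".

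**Tumour assessment.** In the main period, scans are "done at baseline, 8 ± 1 weeks and 16 ± 1 weeks after initiation of study drug administration" (Table 3, footnote f). In the extension they come every 12 weeks (Table 4, footnote d). The final visit is four weeks after drug stops. Its column has no tumour assessment in either table, although it does include physical examination, laboratory tests, medication review, pain and quality of life, and adverse events.

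**Afterwards.** Study procedures ends with the statement that "follow-up survival information will be collected by either clinical visit or telephone contact every 12 weeks", until death.

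**The concern.** A Kaplan-Meier PFS curve needs a progression date, or a defensible censoring date, for every patient. For someone who stops drug without documented progression, the published schedule gives no tumour assessment at the final visit and then only vital status. If progression follows, it is not recorded.

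Kaplan-Meier also assumes that a censored patient has the same future risk as those still followed. A patient withdrawn because the disease is making them worse probably does not. Removing such patients from the risk set without an event would raise the curve and lengthen the median. An analysis rule written later can choose how to treat these patients, but it cannot recover progression dates that were never collected. This is why the point concerns the collection schedule and not merely analysis detail left to another document.

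**Working it through.** **1. The plan's own design, to see what is affected.** "The sample size was calculated according to the Simon’s minimax two-stage design, with PFS at 16 weeks as the primary endpoint". Inputs from Sample size determination: p0 = 0.12, p1 = 0.32, continue if at least 3 of 19 succeed, declare promising if at least 6 of 27 succeed.

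P(promising | p) = Σ over x = 3 to 19 of b(19, x, p) × P(Y ≥ 6 − x), with Y ~ Bin(8, p).

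This gives 0.0936 at p = 0.12 and 0.9000 at p = 0.32, so the stated design reproduces. It counts binary successes. The Kaplan-Meier estimate does not enter it.

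**2. A bound by hand.** Suppose 27 patients, of whom 6 are truly progression-free at week 16. Let c patients who would have progressed be censored before the first event. The Kaplan-Meier value becomes 6/(27 − c):

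- c = 0: 6/27 = 0.222
- c = 3: 6/24 = 0.250
- c = 5: 6/22 = 0.273

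If instead those c patients would all have stayed progression-free, the truth is (6 + c)/27, which is 0.333 for c = 3 and 0.407 for c = 5. The same censoring is then biased downward. The direction depends on who leaves.

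**3. Leaving shortly before progression.** Inputs:

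- n = 27.
- Exponential time to progression with a median of 1.8 months (Sample size justification), about 7.8 weeks.
- Scans at weeks 8, 16, 28 and every 12 weeks after that.
- Assumed, not in the document: a share of patients exits uniformly 0-4 weeks before progression and is censored at the last scan.

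Check with full follow-up: 2^(−16/7.8) = 0.241. From 6,000 simulated trials per row:

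| Share leaving | Mean KM PFS at week 16 | P(reported median falls at week 8) |
|---|---|---|
| 0% | 0.24 | about 0.54 |
| 10% | 0.26 | 0.49 |
| 20% | 0.29 | 0.39 |
| 30% | 0.32 | 0.29 |

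Where the median does not fall at week 8, it moves to a later scan, mostly week 16. With a true week-16 PFS of 0.12, the same shares give about 0.13, 0.15 and 0.17.

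**4. A milder model.** A fraction f leaves uniformly over weeks 0-16 and is censored on leaving. Leavers have k times the hazard h of the others, and h is set so that (1 − f)·exp(−16h) + f·exp(−16hk) equals the true week-16 PFS. Values for f = 10%, 20%, 30%:

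| k | True 0.32 | True 0.12 |
|---|---|---|
| 4 | 0.328, 0.339, 0.353 | 0.122, 0.125, 0.128 |
| 2 | 0.330, 0.338, 0.346 | 0.124, 0.128, 0.133 |
| 1 | 0.32 throughout | 0.12 throughout |
| 0.5 | 0.306, 0.294, 0.283 | 0.107, 0.098, 0.091 |

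**5. Leaving unrelated to progression.** Using step 3 with exits at random over weeks 0-16, mean week-16 PFS stays at 0.24 for 10%, 20% and 30% leaving. The chance of a week-8 median does not fall (0.55-0.58).

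**6. Using a later death as the event.** Sample size justification quotes a median survival of about 6 months against 1.8 months to progression. A death date would usually fall well after the missed progression, so this option also lengthens PFS.

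**The case against.** Several objections have force.

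- **Scans may continue.** Footnote f dates the week-8 and week-16 scans from first dose, not from treatment status, and nothing says they stop with the drug. A reader might infer that only survival is collected once drug stops. That is too strong: early leavers may still be scanned, and the final visit gathers clinical data that could show signs of progression. But the text does not require those scans in leavers, and this footnote cannot help a patient who stops in the extension.
- **Censoring is not stated.** A reader might infer that these patients can only be censored. The single stated rule is for loss to follow-up, and a patient contacted every 12 weeks is not lost. Fuller event and censoring rules may sit in a document not shown. This stands, so the conclusion must be conditional on how they are handled.
- **Toxicity leavers.** A reader might extend the upward bias to patients who stop for toxicity. The documents say nothing about their prognosis, and steps 4 and 5 show no bias when leaving is unrelated to progression and downward bias when leavers do better.
- **The larger figures are built in.** Step 3 makes every leaver exit just before progression, and the 10-30% shares have no source in the document. Deterioration shares a criterion with progression, so some of these patients would be recorded as progressed. The shifts at 10% and 20% (+0.02 and +0.05) are also smaller than the between-trial standard deviation of about 0.08-0.09.
- **Limited consequence.** A reader might infer that the go/no-go decision is compromised. It rests on the binary count, and PFS over time is a descriptive secondary estimate. How to class a patient with no week-16 scan is a separate question.

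What remains is the collection gap. The article publishes two visit tables and a post-treatment follow-up rule, and together they do not provide for recording progression after drug stops.

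**Conclusion.** The concern holds in limited form. After drug stops without documented progression, no tumour assessment is scheduled at the final visit, later follow-up is for survival only, and the status of the week-8 and week-16 scans is unclear for early leavers. Stops during the extension are not covered at all. Later progression is therefore not captured for secondary PFS.

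Upward bias is likely for patients leaving through disease-related deterioration, provided they are censored or a later death is taken as the event. Counting withdrawal as failure would push the other way.

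The size is uncertain. It is roughly 2 to 8 percentage points at week 16 if 10-30% leave within four weeks before progression, and about 1 to 3 points against a true 0.32 if leavers merely have 2-4 times the hazard. Both ranges rest on assumed shares. The Simon operating characteristics (0.0936 and 0.9000) are not directly changed. The gap is still worth closing, because missed progression dates are hard to reconstruct later.

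**What to change.** 1. State in Study procedures that stopping mycophenolate without progression does not end tumour follow-up, and that the week-8 and week-16 assessments in footnote f are kept for such patients unless consent is withdrawn.
2. At the existing 12-weekly survival contact, also record the date and basis of any progression (from routine imaging) and the start of any new anticancer therapy. This also covers patients who stop in the extension.
3. Add a PFS sensitivity analysis that counts withdrawal for disease-related deterioration as an event.

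The cost is a sentence in the protocol, a few fields on an existing contact form, one extra analysis, and one or two already scheduled scans in the few patients who stop early. The drawback is that later progression dates will come from routine and not protocol imaging, so they will be less evenly timed. Sample size and decision rule stay as they are.
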